**Methods and analysis:**

This prospective longitudinal observational study (V.6, 20 September 2023) will be conducted across multiple UK secondary care sites from August 2022 onwards, with an aim to enrol 1000 participants testing positive for RVI. Adults admitted with respiratory symptoms who test positive for RVIs via the BioFire® FilmArray® System or other validated diagnostic PCR tests will be enrolled. The data collected include patient demographics, clinical history, comorbidities and symptoms experienced prior to, during and after hospitalisation with follow-up after discharge at weeks 1, 2, 4, 8, 12 and 26. In addition, biological samples are collected at multiple time points during the hospital stay. The primary endpoints are to study the impact of different RVIs and identify predictors of disease progression and length of stay. Secondary endpoints include time to recovery and healthcare cost. Exploratory endpoints focus on biomarker profiles associated with virus type and clinical outcomes.

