### Variables

#### Primary outcomes

The primary outcomes of the UNIVERSAL study are focused on characterising the clinical impact of RVIs in hospitalised adults. This includes not only documenting the occurrence of various respiratory viruses, including influenza, RSV and SARS-CoV-2, but also a broader range of viruses such as rhinoviruses, parainfluenza viruses and human metapneumovirus. The study aims to evaluate their association with disease severity, progression and recovery. The study also aims to identify clinical and biological predictors of these outcomes, including markers such as viral load, inflammatory markers such as C reactive protein (CRP) and patient demographics. Another key outcome is measuring the duration of hospital stay for patients with RVIs and understanding the factors that contribute to prolonged hospitalisation.

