#### Exposure—RVI

The primary exposure in the study is the presence of a confirmed RVI in hospitalised adults with acute upper or lower respiratory illnesses (eg, rhinitis, rhinosinusitis, pharyngitis, pneumonia, bronchitis and influenza-like illness), including acute exacerbations of chronic respiratory illnesses (such as COPD, asthma or bronchiectasis). This is determined using the BioFire® FilmArray® System or other validated clinical diagnostic PCR-based methods established at clinical sites during the patient’s current hospital admission.

The diagnostic criteria for RVIs in the UNIVERSAL study are based on laboratory confirmation using the BioFire® FilmArray® System or other PCR tests. Clinical diagnoses made by treating clinicians, supported by symptoms and imaging findings, are also used to categorise respiratory illnesses.

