#### Predictors

The study examines a range of predictors that may influence the primary and secondary outcomes. These predictors include demographic factors such as age, sex, ethnicity and socioeconomic status. Clinical history, including pre-existing comorbidities such as COPD, asthma, cardiovascular disease, smoking status and vaccination history, is another important predictor. Clinical presentation at the time of admission, including symptoms, severity scores such as the National Early Warning Score 2 (NEWS2)^6^ and initial laboratory and imaging findings, are also critical predictors.

By clearly defining these variables, the UNIVERSAL study aims to provide comprehensive insights into the phenotypic diversity, disease progression and economic impact of RVIs in hospitalised adults. This detailed analysis will contribute to the development of targeted interventions and improve patient outcomes

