#### Demographic and clinical data

Demographic and clinical data are sourced from patient interviews and medical records. Detailed demographic information, including, sex, age at enrolment, height, weight, ethnicity, postcode, number of people in household and smoking history, is collected through structured patient interviews conducted by trained research staff. Medical history, including pre-existing comorbidities and vaccination history, is obtained from patient interviews and verified against medical records. Clinical presentation data, encompassing symptoms, duration of illness and severity scores such as the NEWS2 and OSCI, are documented using standardised assessment tools. Length of stay is addressed through review of clinical discharge summaries. During the discharge visit, details of treatments received during admission including time spent on intensive care or high dependency are collected from medical records. Mortality and readmission data are collected through medical records and patient interviews. While socioeconomic factors are not a primary focus of the study, participant postcodes are collected to allow for area-based deprivation analyses (eg, linkage to the Index of Multiple Deprivation).

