### Statistical methods

A detailed statistical analysis plan has been designed for the UNIVERSAL study involving all statistical considerations to ensure robust and reliable results. Here, we will only describe the essential statistical methods for the primary analysis. For analysis involving multiple comparisons, we will adjust them with Bonferroni correction. SAS V.9.4 or above, STATA V.18 or above and R V.4.4 or above will be used for analyses.

Descriptive statistics will be used to summarise baseline characteristics, clinical presentation and outcomes related to different viral pathogens. Measures of central tendency (mean, median) and dispersion (SD, IQR) will be calculated for continuous variables, while frequencies and percentages are used for categorical variables. Univariate analyses will be used to explore the relationship between key characteristics and the outcome measures. Clustering techniques will be used to explore similar patterns with respect to symptoms, severity and duration.

Multivariable regression models will be employed to identify associations between key predictors and outcomes while controlling for potential confounders. These models will be adjusted for demographic factors (age, sex, ethnicity, socioeconomic status, vaccination status), clinical variables (severity scores, comorbidities) and treatment regimens. Prior to model fitting, multicollinearity among covariates will be assessed using appropriate statistical methods (eg, variance inflation factor), and adjustments will be made if necessary to ensure model stability. The choice of regression model (eg, logistic regression for binary outcomes, linear regression for continuous outcomes) depends on the nature of the dependent variable. For analysis involving data at multiple time points, multilevel regression with first-level autoregressive error correlation structure (ie, AR(1)) will be used to control for within-subject correlation.

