#### Subgroup and interaction analyses

Subgroup analyses are conducted to explore differences in primary and secondary outcomes among specific patient groups, such as those with different respiratory viruses (eg, influenza, RSV, SARS-CoV-2) or varying severity levels. Interaction terms are included in regression models to examine potential interactions between key variables, such as the interaction between age and comorbidities in predicting disease severity. We will also consider stratifying the analysis by different respiratory viruses if the sample size allows. These analyses help identify variations in treatment effects and outcomes across different subpopulations.

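### One covariate set treats severity scores and treatment as confounders in every outcome model, so the virus models do not estimate the overall association of virus with outcome

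*Protocol article*

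**What the plan says.** All references are to the Protocol article.

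- **Statistical methods.** The section says it sets out the essential methods for the primary analysis. On the regressions it says: "Multivariable regression models will be employed to identify associations between key predictors and outcomes while controlling for potential confounders". It continues: "These models will be adjusted for demographic factors (age, sex, ethnicity, socioeconomic status, vaccination status), clinical variables (severity scores, comorbidities) and treatment regimens". No score, time point or exception by outcome is given. Univariate analyses are also planned.
- **Abstract, Methods and analysis.** "The primary endpoints are to study the impact of different RVIs and identify predictors of disease progression and length of stay".
- **Primary outcomes.** Of the respiratory viruses: "The study aims to evaluate their association with disease severity, progression and recovery". Length of stay and its contributing factors are added as a further key outcome.
- **Exposure—RVI.** "The primary exposure in the study is the presence of a confirmed RVI in hospitalised adults".
- **Predictors.** Admission severity is listed as a predictor: "Clinical presentation at the time of admission, including symptoms, severity scores such as the National Early Warning Score 2 (NEWS2").
- **Data collection.** The initial treatment regimen is recorded on admission. OSCI and treatment updates are recorded through the stay. At the discharge visit, "details of treatments received during admission including time spent on intensive care or high dependency are collected from medical records" (Demographic and clinical data).
- **Subgroup and interaction analyses.** An age-by-comorbidity interaction in a model for disease severity is given as an example. The section closes: "These analyses help identify variations in treatment effects and outcomes across different subpopulations".

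**The concern.** A confounder of virus and outcome has to act before, or independently of, the infection. Age, sex, ethnicity, deprivation, comorbidity and vaccination status do. A severity score taken once the patient is admitted with the infection is at least partly produced by it, and treatment responds to the pathogen and to how ill the patient is. If one virus lengthens stay because it makes patients sicker, a model that holds sickness fixed removes that contribution.

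At stake is the comparison between viruses, a headline aim. Viruses could look alike in the adjusted models because the severity differences between them had been adjusted away. There is also a plain inconsistency: severity stands on the outcome side in Primary outcomes and on the covariate side in Statistical methods.

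The same list also has to serve models that identify predictors of progression and length of stay. There admission severity is a proper predictor, but treatment given later is not known when a prediction is made from admission.

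**Working it through.** **Plan's own figures.** The plan gives no effect size for virus, severity or treatment, so there is no figure on this point to reproduce. Its sample-size figures are not in dispute. The precision figure reproduces: 1.96 × √(0.25/1000) = 3.1% and 1.96 × √(0.25/2000) = 2.2%.

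**Step 1: order of events.**

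| Variable | When recorded | Role in Statistical methods | Other role |
|---|---|---|---|
| Age, sex, ethnicity, deprivation, vaccination, comorbidity | Precede infection | Covariate | Predictor |
| Severity scores | Admission (NEWS2), daily in hospital (OSCI) | Covariate | Primary outcome; predictor |
| Treatment | Admission, during stay, discharge | Covariate | None stated |

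Severity and treatment are nowhere recorded before the infection.

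**Step 2: illustration.** All values here are assumptions. Virus V (two groups of equal size) raises severity S by a = 0.5. S raises a continuous outcome Y, such as log length of stay, by b = 0.4. The direct effect of V on Y is d = 0, 0.1 or 0.2. An unmeasured frailty U enters both S and Y with coefficient u = 0, 0.5 or 0.8. Treatment depends on S and changes Y by -0.3, 0 or +0.3. A measured covariate has coefficient 0.3 in both equations and is always adjusted for. Residual SDs are 1, with 1,000,000 simulated patients per scenario.

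Without S and treatment in the model, and with no treatment effect, the V coefficient is d + a·b = d + 0.5 × 0.4 = d + 0.20. The treatment settings move this by about 0.025 either way.

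With S in the model, the V coefficient is d − a·u²/(1 + u²):
- u = 0: d − 0
- u = 0.5: d − 0.5 × 0.25/1.25 = d − 0.10
- u = 0.8: d − 0.5 × 0.64/1.64 = d − 0.195

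Simulated results:

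| Direct effect d | Total effect (no S, no treatment) | With S and treatment, u = 0 | u = 0.5 | u = 0.8 |
|---|---|---|---|---|
| 0 | 0.17 to 0.22 | 0.00 | -0.10 | -0.20 |
| 0.1 | 0.27 to 0.32 | 0.10 | 0.00 | -0.10 |
| 0.2 | 0.37 to 0.42 | 0.20 | 0.10 | 0.00 |

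**Step 3: reading.** With no unmeasured common cause, adjustment leaves exactly the direct effect and never changes the sign. With one, the estimate is negative in three of the six combinations, about zero in two and positive in one. Treatment here depends on severity alone, so adding it once S is in the model changes nothing. The exercise does not cover treatment chosen directly by virus.

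**Step 4: do the univariate analyses fill the gap?** No. They leave age, comorbidity and vaccination uncontrolled. No stated analysis adjusts for pre-infection factors alone.

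**The case against.** The case on the other side is substantial.

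- **The target is not spelled out.** The named exposure is confirmed infection, not virus type, and the regression text speaks of key predictors without naming virus as a model term. A severity-adjusted association is a legitimate quantity. This stands in part: calling the estimates biased is right only for the overall association of virus with outcome. But the abstract and Primary outcomes do make the different viruses' impact a primary matter.
- **Admission severity belongs in progression models.** This stands in full. It is why the list needs splitting, not simply shortening.
- **Timing may be settled in the unseen analysis plan.** The sentence gives no timing, and treatment could mean the initial regimen. This stands as to detail. It does not remove the problem, since even the earliest recorded values follow the infection, and the article affirmatively fixes the list.
- **Severity scores may partly reflect chronic disease, and age and comorbidity would capture some frailty.** Both are true, and both limit the effect.
- **Everyone was admitted.** The cohort is already selected on being ill enough for admission, so dropping severity does not give a clean total effect. This also stands.

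A reader might infer three stronger things that the documents do not support. First, that the virus estimates will reverse: this needs an assumed unmeasured factor and a small or absent direct effect. Second, that the clinical prediction model in Sample size calculation will use later information: nothing says that model uses this list. Third, that intensive-care time is a covariate: it is listed only as a collected item.

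**Conclusion.** The point holds in a limited form. A single covariate set labels as potential confounders two kinds of variable that are at least partly consequences of the infection, and one of them is also a primary outcome. For the virus-to-outcome question, the models as written do not estimate the overall association. They tend to shrink it towards the direct effect, and could reverse it if strong unmeasured common causes of severity and outcome exist.

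The size is not known. The movement from 0.17–0.42 to between -0.20 and +0.20 illustrates the mechanism under invented coefficients and is not an estimate for this study. The conclusion rests on two readings: that the listed models include those comparing viruses, and that the severity scores and treatments meant are the ones described under data collection. No sample-size figure is affected. It is worth correcting before analysis but does not put the study at risk.

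**What to change.** In Statistical methods, replace the single list with two.

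1. **Virus-to-outcome models.** The main analysis adjusts for pre-infection factors only: age, sex, ethnicity, deprivation, comorbidities and vaccination status. Severity- or treatment-adjusted virus estimates are reported as labelled secondary analyses, with the score and time point named. Severity is never a covariate where severity is the outcome.
2. **Models predicting progression or length of stay from admission.** Admission severity is allowed; treatment given after the prediction time is excluded.

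As a minor wording point, remove the reference to treatment effects from the last sentence of Subgroup and interaction analyses. Treatment is not assigned in this observational study, and no treatment comparison is described there.

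The cost is wording and one extra set of models; no new data are needed. The virus estimates stay conditional on hospital admission, and the report should say so.

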#### Subgroup and interaction analyses

Subgroup analyses are conducted to explore differences in primary and secondary outcomes among specific patient groups, such as those with different respiratory viruses (eg, influenza, RSV, SARS-CoV-2) or varying severity levels. Interaction terms are included in regression models to examine potential interactions between key variables, such as the interaction between age and comorbidities in predicting disease severity. We will also consider stratifying the analysis by different respiratory viruses if the sample size allows. These analyses help identify variations in treatment effects and outcomes across different subpopulations.

#### Missing data

Missing data are handled using multiple imputation techniques to ensure that the analyses remain robust and unbiased. This approach involves creating several imputed datasets where missing values are estimated based on observed data. Specifically, we will use the Additive Regression, Bootstrapping and Predictive Mean Matching (*aregImpute*) function in *R* package *Hmisc*^11^ to conduct at least five multiple imputations. The results from these datasets are then combined to produce final estimates. Sensitivity analyses are performed to assess the impact of analysis methods with and without imputation on the primary study findings.

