#### Loss to follow-up

Loss to follow-up is addressed through diligent follow-up procedures, including regular contact with participants via phone calls, electronic surveys and in-person visits, as laid out in the SCTU DMP. The reasons for and extent of loss to follow-up are documented, and statistical methods, such as missing data imputation described above, are used to account for the impact of censored data on study outcomes. This helps maintain the integrity of the dataset and ensures valid and reliable results.

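### The named additive imputation model is narrower than the planned interaction analyses; if it is pooled across groups, interaction estimates shrink partly towards zero, mainly for follow-up outcomes

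*Protocol article*

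**What the plan says.** The Missing data section of the protocol article names one method for all analyses: "we will use the Additive Regression, Bootstrapping and Predictive Mean Matching", run "to conduct at least five multiple imputations". It mentions no product terms, no imputation within virus group and no exception for particular analyses. The Loss to follow-up section extends the method to attrition: "statistical methods, such as missing data imputation described above, are used to account for the impact of censored data on study outcomes". Outcomes as well as covariates may therefore be imputed.

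The Subgroup and interaction analyses section says "Interaction terms are included in regression models to examine potential interactions between key variables", and gives the example "such as the interaction between age and comorbidities in predicting disease severity". It adds a conditional plan: "We will also consider stratifying the analysis by different respiratory viruses if the sample size allows".

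One check is planned, under Missing data: "Sensitivity analyses are performed to assess the impact of analysis methods with and without imputation on the primary study findings".

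The Statistical methods section says that a detailed analysis plan exists and that the article gives only the essential methods for the primary analysis. For repeated measurements it names multilevel regression with AR(1) errors.

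**The concern.** An additive imputation model predicts each incomplete variable from a sum of separate terms, so a predictor has the same effect whatever the level of the others. An interaction analysis asks whether that is false. When outcomes are imputed from a pooled additive model, the imputed records are generated as though the answer were already no. Mixing them with the observed records dilutes any real interaction.

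Heterogeneity among patients is the primary objective, and recovery is among the primary outcomes. Recovery questionnaires run to week 26, and the Discussion accepts that some attrition is inevitable. Real differences between patient groups in how predictors act could be understated in the data most exposed to loss. Main effects of virus are not at issue, provided virus is in the imputation model.

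**Working it through.** The article states no figure on this point, so there is none to reproduce.

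**Inputs from the article.** n = 1000 (Sample size calculation); additive regression, bootstrap and predictive mean matching, at least five imputations (Missing data); product terms in the analysis (Subgroup and interaction analyses).

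**Assumed inputs.** 10-40% missing at random; a continuous outcome; a binary group holding 40% of participants. The true interaction is 0.25 SD per SD in set-up A and 0.4 in set-up B. A also has a variant with a fully observed earlier wave, correlated about 0.6 with the outcome given covariates.

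**Step 1: a simple rule.** Let f be the fraction of outcomes imputed and c the share of the interaction that imputed records still carry. If missingness is spread roughly evenly, the share retained is (1 - f) + f·c = 1 - f(1 - c).

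- No earlier wave: c = 0, so the share is 1 - f.
- Earlier wave showing the same interaction, correlation 0.6: c is about 0.6, so the share is 1 - 0.4f.

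**Step 2: simulation.** Share of the interaction retained under pooled additive imputation:

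| Scenario | 10% | 20% | 30% | 40% |
|---|---|---|---|---|
| Outcome missing, no earlier wave: rule | 0.90 | 0.80 | 0.70 | 0.60 |
| Same, set-up A | 0.91 | 0.82 | 0.75 | 0.66 |
| Same, set-up B | 0.91 | 0.85 | 0.73 | 0.65 |
| Outcome missing, earlier wave: rule | 0.96 | 0.92 | 0.88 | 0.84 |
| Same, set-up A | 0.96 | 0.92 | 0.89 | 0.84 |
| Predictor missing, set-up A | 0.92 | 0.86 | 0.79 | 0.71 |
| Predictor missing, set-up B | 0.94 | 0.87 | 0.81 | 0.74 |

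A used 400 replicates and 10 imputations and is relative to the full-data estimate. B used 300 replicates, 5 imputations and spline terms and is relative to the truth, with Monte Carlo standard error about 0.01. Both copied the named method with five donors; the R function itself was not run.

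A third simulation gave about 0.89 falling to 0.61 between 10% and 40% missing without an earlier wave, and 0.94 falling to 0.80 with one. The last value fits c = 0.5 in the rule: 1 - 0.4 × 0.5 = 0.80.

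Taking the extremes for missing outcomes: with an earlier wave, the loss runs from 1 - 0.96 = 4% to 1 - 0.80 = 20%; without one, from 1 - 0.91 = 9% to 1 - 0.61 = 39%.

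**Step 3: does a different imputation model repair it?** At 10/20/30/40% missing:

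- Imputing within group levels (B): 0.99/1.01/0.98/0.97 with the outcome missing, 1.01/1.00/1.00/1.00 with the predictor missing.
- Adding a product term, outcome missing without an earlier wave: 0.99/0.98/0.98/0.98 (A) and 0.99/1.00/0.97/0.95 (B).
- Adding a product term, predictor missing: 0.98/0.95/0.91/0.89 (A) and 0.96/0.92/0.89/0.84 (B), so only a partial repair.

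Complete-case estimates stayed within about 2% of the reference in both set-ups. That reflects the missingness mechanisms simulated and is not a general property.

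**Step 4: scale against sampling error.** In set-up A the full-data standard error of the interaction is about 1/√(1000 × 0.4 × 0.6) = 0.065. A 10% bias is 0.025, or about 0.4 of a standard error. A 20% bias is 0.05, about 0.8. A 39% bias is 0.0975, about 1.5.

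**The case against.** The strongest reply is that the article condenses a fuller analysis plan. It names a function and a minimum number of imputations; it does not list the terms in the imputation model or say whether imputation is pooled. Imputing within virus group could use the same function and would contradict nothing stated. This stands as a limit on the point, which is conditional on pooling without product terms. It does not remove it: the method is named without qualification beside analyses that an additive model cannot represent.

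Several stronger readings are tempting and are not supported.

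- *A reader might infer that imputed values carry no interaction at all.* That is so only for outcomes imputed without an earlier wave. At 40% missing it would leave about 60% of the effect, yet 71-74% remains with a missing predictor and 80-84% with an earlier wave.
- *A reader might infer that the article's own example is badly affected.* Age and comorbidities are collected at enrolment, with medical history verified against records, and the ordinal clinical score is recorded daily in hospital. Little missingness is likely there.
- *A reader might infer that virus-stratified results are certain to be biased.* Stratification is only to be considered if numbers allow, and the bias arises only if imputation is pooled across viruses.
- *A reader might infer a large loss of power.* In set-up A power was 56%, against 82% with the interaction in the imputation model. That is at 40% missing with no earlier wave, which fits poorly a study with six follow-up points and a planned multilevel model.

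The comparison with and without imputation also has some force, since it could expose a discrepancy. But it is limited to the primary findings, and it neither corrects the estimate nor says which result to trust.

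**Conclusion.** The point holds in a conditional form and should be corrected; it is not a fatal flaw. As described, the imputation model is narrower than the interaction analyses. If it is pooled across groups with no product terms, a true interaction is pulled partly towards zero.

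The direction was the same in every scenario simulated with missing data. The size depends on a missing-data rate that the article does not give. The 4-20% range (earlier wave in the imputation model) is the more relevant one for the repeated questionnaires; 9-39% applies when no earlier wave is used. Both rest on the assumed 10-40% missing at random and, in the set-ups described, on a continuous outcome and a 40% subgroup. The concern is mainly about follow-up outcomes subject to attrition.

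**What to change.** In the Missing data section, keep aregImpute for main-effect models and add that:

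1. interaction and virus-stratified analyses will impute within the relevant virus or factor groups, merging small groups, or will use an imputation model compatible with the planned interaction. A plain product term is not a full repair when a predictor is missing;
2. where only a repeated outcome is missing, the multilevel model already planned will be fitted to all observed visits without imputing the outcome;
3. the comparison with and without imputation will also cover the interaction results.

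The cost is wording and some extra programming, with no new data or participants. The downside is slightly wider intervals for interaction terms. Some small virus groups will need merging, because imputing within them with many covariates may be unstable.
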